## Abstract

**Background:**

Although probiotics have been shown to improve constipation-related symptoms, a clear consensus on the use of probiotics as a constipation-relieving agent has not been reached, which is attributed to the limited available evidence and inconsistent protocols used in existing studies.

**Method:**

A randomized, double-blind, placebo-controlled clinical trial is designed to study the efficiency and possible mechanism of action of probiotics for chronic constipation, in which 200 eligible volunteers with chronic constipation will be randomly assigned to a probiotic group (oral *Lactobacillus plantarum* P9 probiotic powder, 100 billion colony-forming units (CFUs)/day) or a placebo group. Volunteers, treatment distributors, data collectors, and data analysts will be blinded. The primary outcome is the weekly mean frequency of complete spontaneous bowel movements (CSBMs), and secondary outcomes include weekly mean frequency of CSBMs ≥3, weekly mean frequency of spontaneous bowel movements (SBMs), weekly mean stool appearance score, weekly mean difficulty of passing stool score, weekly percentage of volunteers who use auxiliary measures to assist with defecation (WPUAMA), quality-of-life (QOL) score, emotional status score, gut microbiome, and faecal metabolome. Each outcome measure will be assessed at the time points of preadministration (day 0), administration (day 14 and/or 28), and postadministration (day 42) to identify inter- and intragroup differences. Adverse events will be recorded to evaluate the safety of *L. plantarum* P9. *Discussion*. The protocol will provide methodological guidance for other similar studies, avoiding methodological bias and ultimately facilitating the formulation of consensus on the use of probiotics as a constipation-relieving agent. In addition, the results are more comprehensive than those of existing studies and may objectively and scientifically reflect the effectiveness of *L. plantarum* P9 on constipation. If the expected study findings are obtained, *L. plantarum* P9, taken as a probiotic, may become a complementary choice for chronically constipated patients. This trial is registered with Chinese Clinical Trial Registry (ChiCTR) (no. ChiCTR2000038396) registered on November 22, 2020, https://www.chictr.org.cn/showproj.aspx?proj=54024.

## 1. Background

Constipation is a common diagnosis made by gastroenterologists based on the assessment of infrequent bowel movements (<3 per week) and difficult stool passage, while patients may report multiple symptoms, including a sense of incomplete defecation, abdominal pain, bloating, excessive straining accompanied by a sensation of anorectal blockage during stool passage, and requiring manual assistance to release the stool. Acute (or nonchronic) constipation either results in blockage of the intestinal tract that requires surgery [1] or tends to be ignored by patients. Academically, constipation always refers to chronic constipation, which is categorized into primary constipation and secondary constipation (attributed to other diseases or factors). Based on the Rome IV criteria [2], the classifications of primary constipation are functional constipation, irritable bowel syndrome with constipation, and defecatory disorders. From the aspect of the transiting rate of stool movement through colonic and contraction of muscle tissue during defecation, primary constipation is also divided into slow transit constipation, normal transit constipation, and defecatory disorders [3].

The global prevalence of constipation ranges from 10% to 30% [4–7]. The variance in prevalence may be attributed to the individuals assessed in different surveys, which may be self-reported or use different Rome criteria (I, II, III or IV) to identify participants [5, 8–10], thus lacking a concise definition of constipation. Overall, chronic constipation is more frequent in the population with the following characteristics: elderly, female, nonwhite race, medication intake, low income and education level, physical inactivity, and depression [8, 11–23]. Because patients are constantly suffering from physical symptoms and psychological distress, chronic constipation potentially disturbs people's lives, studies, and work [24, 25] due to dyspareunia, sexual dysfunction, urine retention [26], reduced mental health and social function [24, 27], school absenteeism, a high number of lost work days, and the cost of medical care [28].

Only one-fifth of patients with constipation seek medical advice [19], and laxatives are the most frequently prescribed agents [29, 30]. Laxatives, physical exercise, fibre intake, and dietary management are the traditional treatments. However, approximately 50% of constipated individuals are dissatisfied with their current treatments [31, 32]. As many as 74% of nursing home residents have been reported to use laxatives daily [33–35], of which only 28%–57% are estimated to be satisfied with the treatment according to the results of two Internet-based surveys [36, 37]. Undesirable side effects are a main reason for suboptimal satisfaction. New treatments must be developed for unsatisfied patients, and daily intake of probiotics holds great promise since various probiotics have shown benefits for constipation treatment [38–43].

However, although many studies have reported that probiotics are potentially beneficial for constipated individuals [39–43], a clear consensus on the use of probiotics as a constipation-relieving agent has not been reached [44]. This lack of consensus is mainly attributed to the shortage of study methodology in terms of incorrect statistical analysis, inconsistent definitions of constipation and outcomes of the intervention, and an unvalidated assessment technique [44–46]. Therefore, high-quality randomized controlled trials (RCTs) are needed to reach a more confident consensus [47]. Moreover, RCTs examining the effectiveness of probiotics as a constipation-relieving agent may elucidate a clear mechanism of action for a more confident conclusion. Generally, a balanced intestinal flora provides health benefits to human hosts; conversely, an imbalanced flora may promote the development of constipation [48]. Consistently, probiotics may positively modify the intestinal flora [49, 50] and even provide potentially beneficial microorganisms to the host.

Thus, we designed this protocol to study the effectiveness of *L. plantarum* P9 on chronic constipation and to guide other studies assessing the effectiveness of probiotics. The correlation between the clinical improvement of symptoms and changes in intestinal flora was also analysed.

## 2. Methods and Design

### 2.1. Design

This study is a randomized, double-blind, placebo-controlled clinical trial conducted in Nanchang, China, and volunteers may receive the intervention (oral probiotics or placebo) in their own homes. The protocol was prospectively registered at the Chinese Clinical Trial Registry (ChiCTR) (NO. ChiCTR2000038396) (Appendix 1) and approved by the Ethics Committee of the First Affiliated Hospital of Nanchang University (Approval Number: IIT [2020], Clinical Ethics Review NO. 004) (Appendix 2). This manuscript is prepared according to the Standard Protocol Items: Recommendations for Interventional Trials (SPIRIT) [51]. The flowchart of the trial process is provided in Figure 1.

### 2.2. Inclusion Criteria

Eligible patients should fully meet the Rome IV criteria [2]:(1)Onset of the following symptoms for at least 6 months before enrolment and symptoms within the past 3 months that meet the following criteria [2, 52]:Two or more of the following symptoms: (a.) difficulty passing stool, at least 25% of defecations; (b.) lumpy or hard stool, at least 25% of defecations (Bristol Stool Form Scale (BSFS) types 1 or 2 (Appendix 3) [53]); (c.) incomplete defecation in at least 25% of defecations; (d.) sense of anorectal obstruction in at least 25% of defecations; (e.) need for manual assistance for defecation (such as using fingers to assist with defecation or pelvic floor support) in at least 25% of defecations; and (f.) fewer than 3 spontaneous bowel movements (SBMs) per week.Loose stool rarely occurs without the use of laxatives.Insufficient stools are rarely present without the use of laxatives.(2)Willing to sign the informed consent form (Appendix 4)(3)The volunteers involved in this study will be patients with chronic constipation aged 18–65 years. For patients aged from 18 (exclusive) to 50 (inclusive) years, the result of stool tests (including occult blood) conducted during the screening period must be normal or abnormal but determined to be clinically irrelevant by the investigators. For patients aged 50 (exclusive) to 65 (inclusive) years, the result of a colonoscopy performed at a tertiary or higher-level hospital within the past 6 months must be normal or abnormal but determined clinically irrelevant by the investigators.

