### 2.12. Sample Size

This study is a clinical trial during which volunteers will consume a sample medication or placebo for 28 days and will be followed up for 42 days. The primary outcome measure is the weekly frequency of CSBMs. The expected weekly frequencies of CSBMs on day 28 are 1.1 in the control group and 4.1 in the probiotic group, with a between-group difference of 3. Given a standard deviation *S* = 6, *α* = 0.05, and *β* = 0.20, the sample size should be at least 63 volunteers per group, as calculated with the formula for statistically significant effectiveness. After considering the drop-out rate (20% or lower), the sample size should be 76 or more participants per group. The final sample size will be 100 participants per group for a total of 200 volunteers.

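### A mandatory inclusion line in Section 2.2, read literally, excludes volunteers who qualify through infrequent stools under item (f)

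*Protocol article*

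**What the plan says.** Section 2.2 (Inclusion Criteria) opens with "Eligible patients should fully meet the Rome IV criteria" and then sets out the symptom conditions. The first is "Two or more of the following symptoms", chosen from six labelled (a) to (f); item (f) is "fewer than 3 spontaneous bowel movements (SBMs) per week". Two further lines follow, and neither is offered as an alternative. One is "Loose stool rarely occurs without the use of laxatives". The other is "Insufficient stools are rarely present without the use of laxatives".

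Four other places bear on how that last line works:

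- Section 2.9 defines a spontaneous bowel movement (SBM) as one achieved with no drug or other aid in the preceding 24 hours.
- Section 2.4 bars constipation remedies during a 14-day screening period with a daily diary, and uses that diary to choose eligible volunteers.
- Section 2.3 excludes people who need constipation medicine on a long-term basis.
- Section 1 describes the diagnosis of constipation in terms of fewer than three movements a week together with difficult passage.

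**The concern.** Item (f) treats too few unaided stools as a reason to admit a volunteer. The last line appears to require that too few stools be uncommon when no laxative is taken. Both stand in the same list, and volunteers are asked to meet that list in full.

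A screener who follows the text turns away volunteers with infrequent stools and keeps those who have the other symptoms at adequate frequency. A screener who sets the line aside is working to something other than the printed criterion, and the report would not show which was done. At stake is the description of the enrolled population. This weighs more here because the Discussion adopts Rome IV so that researchers do not define constipation for themselves, and offers the protocol as guidance for other studies. Anyone reusing the text would carry the conflict forward.

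**Working it through.** The plan gives no figure on this point, so there is none to reproduce. The check sets the clauses side by side and then counts the combinations affected.

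**Step 1. Is the line mandatory?** Yes. Section 2.2 asks for the criteria to be met in full, and only the six symptoms fall under the two-or-more rule. The two lines about what is rare without laxatives stand outside that rule.

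**Step 2. Do (f) and the line describe the same state?** By the Section 2.9 definition, (f) concerns stools passed without drugs or aids. The disputed line concerns stools passed without laxatives. During the run-in no constipation remedy is allowed, so both would be judged from the same diary.

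**Step 3. Can both be met?** Take a volunteer with 1 or 2 SBMs a week in the run-in. Item (f) is met. If insufficient stools means too few stools on the same count, the diary shows that they are regularly present without laxatives, so the line fails. One narrow exception exists. An SBM also excludes movements made with non-drug aids, so a volunteer whose movements are mostly manually assisted could have few SBMs but enough movements in total. That volunteer could meet both if the line counts all movements. The text does not say which count applies.

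**Step 4. How much of the eligibility rule is affected?** The inputs are six symptoms, with at least two required.

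- All qualifying combinations: 2^6 − 1 (none) − 6 (one only) = 64 − 7 = 57.
- Combinations that include (f), which need at least one of the other five: 2^5 − 1 = 31.
- Combinations without (f), which need at least two of the other five: 2^5 − 1 − 5 = 26.
- Check: 31 + 26 = 57.

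Under the plain reading the 31 are blocked and the 26 are not necessarily blocked. If the undefined term also took in incomplete defecation (item c), only combinations of (a), (b), (d) and (e) would remain: 2^4 − 1 − 4 = 11.

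These are counts of symptom combinations. They cannot be turned into a share of volunteers, because the article does not say how many present with (f).

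**Step 5. Does any other text resolve it?** No. The term is not defined elsewhere. The companion line on loose stool fits a constipated population; this one does not fit beside (f) or beside the description in Section 1.

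**The case against.** The best defence is that this is a wording slip in a condensed article. Section 2.2 cites an external standard, and Section 2.4 has clinical specialists confirm eligibility at a consultation, so they may well have applied that standard and never excluded anyone on this line. That is plausible, and nothing in the article shows that a volunteer was wrongly turned away. But the line is printed as an operative criterion, the intended text cannot be recovered from the article, and the article does not say which wording was used. This is a conflict between two printed clauses, not a detail left to a fuller document.

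It is also fair to say that the comparison between arms is safe. Screening precedes randomisation, so both arms pass through the same filter. That stands.

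A reader might infer more than the article supports, in four ways:

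- **That the line shuts out the trial's whole target population.** It does not. Item (f) is one of six optional symptoms, and volunteers who qualify on (a) to (e) with 3 or more SBMs a week could still enter.
- **That the typical volunteer fails the line.** Section 2.12 says "The expected weekly frequencies of CSBMs on day 28 are 1.1 in the control group and 4.1 in the probiotic group", but 1.1 is an expected placebo-arm figure at day 28 and counts complete movements. Item (f) counts SBMs, which need not be complete, and the article gives no SBM frequency at screening.
- **That literal screening removes the volunteers whose primary outcome has room to improve.** Volunteers admitted on (a) to (e) can also have few complete spontaneous movements, since incomplete or assisted ones do not count.
- **That the result cannot be attributed because irritable bowel syndrome with constipation is neither included nor excluded.** Section 1 lists it among three classes of primary constipation, but Section 2.2 and Table 2 claim a population with chronic constipation, not functional constipation alone. It is a separate matter and does not bear on this conflict.

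**Conclusion.** The inclusion criteria contradict themselves as written. On the plain reading, the mandatory line excludes volunteers with infrequent stools whom item (f) is meant to help qualify. It blocks 31 of the 57 qualifying symptom combinations and leaves volunteers with 3 or more SBMs a week who have at least two of (a) to (e). The number of people affected cannot be derived from the article.

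This rests on two assumptions: that the undefined term means too few stools, and that it is judged on the same count as (f). A different definition could narrow or widen the conflict, but the article supplies none.

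The consequence is uncertainty about which population was enrolled. Treatment-effect bias does not follow, and no sample-size or power figure depends on this line. Correction is still useful: Section 3.1 reports 130 enrolled against a target of 200, so 200 − 130 = 70 were still to be enrolled at the time of writing.

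**What to change.** 1. Reconcile the line with item (f). The sponsor should compare it with the criteria it cites and then correct or remove it. If the term for insufficient stools is kept, define it and say which movements it counts. The replacement text has to come from the sponsor's source, since the article does not contain it.
2. State which wording was used in the registration questions, at the specialist consultation and at the end-of-run-in review for the 130 volunteers already enrolled.
3. Using the registration answers and run-in diaries collected under Section 2.4, report how many enrolled volunteers do not meet the corrected wording.
4. If there are any, add a sensitivity analysis of the primary outcome without them. The check uses only data from before randomisation, so this exclusion does not depend on treatment. If there are none, say so; no further analysis is needed.

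The cost is a one-sentence amendment and a desk check of screening data already collected, plus one extra analysis only if step 3 finds anyone. No new data collection is required.

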### 2.3. Exclusion Criteria

Volunteers with any of the following conditions will be excluded:Personal or family history of colon cancer, celiac disease, or inflammatory bowel diseaseIntestinal organic diseases confirmed on a previous colonoscopyPlans to become pregnant or father a child in the next 3 months, or pregnant, or breastfeedingAllergies to samples or ingredientsUse of antibiotics or probiotics within the past two weeksUse of antianxiety, antidepressant, or other psychotropic drugs within the past monthNeed for long-term use of medications for constipationHistory of severe diseases, such as myocardial infarction, cerebral infarction, and malignant tumour, judged by the investigators as disqualifying conditionsMajor mental illnesses, inability to control one's actions, or inability to cooperateIlliteracy, inability to understand the informed consent form, or inability to independently sign the informed consent form

### 2.4. Volunteer Recruitment

The investigators will recruit volunteers from the public through in-person communication, posters, and WeChat promotions. Volunteers can scan a WeChat two-dimensional (QR) code to register for enrolment, submit their personal information, and answer questions related to inclusion and exclusion criteria. Volunteers will undergo a procedure that includes three rounds of screening. First, the investigators will collect and collate the volunteers' registration information and, according to the information provided by registrants, invite potentially eligible candidates to participate in a central consultation with clinical specialists for further screening and selection of eligible volunteers. Second, during the central consultation, trained study implementers will introduce the trial to volunteers in the form of a video and information sheets describing the main aspects of the trial and discuss the information provided in the video and information sheets. Then, volunteers will meet with the clinical specialist to confirm their registration information, especially regarding inclusion and exclusion criteria. Third, volunteers will sign an informed consent form in the presence of a member of the data management team (DMT). Then, volunteers will undergo a 14-day screening period when they will not be allowed to take any medicines or health products to improve their constipation symptoms. Each volunteer will be asked to collect one stool sample and complete an online diary entry daily (Figure 2). At the end of the screening period, the diary and stool sample results will be reviewed and used to select eligible volunteers. Subsequent steps will include the formal intervention and follow-up visits (Figure 1).

### 2.5. Randomization and Blinding

Eligible volunteers will be assigned a unique serial number (e.g., 001, 002, 003, 004, 005……). The unique number will be used as the volunteers' ID throughout the study period to guarantee anonymity and confidentiality. For each of these unique numbers, a random sequence will be generated by the computer software *R* 4.1.0 and used to randomly assign the unique number (participant) to the probiotic group or the placebo group. During the study, the volunteer's treatment distributors, data collectors, and data analysts will be blinded to the randomization sequence. The randomization sequence will be maintained by an independent project administrator and will only be unblinded in the case of major safety issues or when performing the interim and final data analyses. Moreover, an independent project administrator will label the probiotics or placebo packages with unique numbers corresponding to random sequences in advance to achieve allocation concealment. During the period of administration, the distributor will distribute the treatment packages according to the unique number that corresponds to each participant.

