### 2.8. Primary Outcome

A defecation diary developed with reference to the literature [32, 53–56] will be completed daily online by the participants (Figure 2). Based on the diary, the changes in primary and some of the secondary outcomes from day 0 (week 0) to day 42 (week 6) will be evaluated.The primary outcome measure is the weekly mean frequency of complete spontaneous bowel movements (CSBMs) [32, 54, 55].

A CSBM is defined as the ability to achieve a complete bowel movement without the use of any drugs or other auxiliary measures during the previous 24 hours. Based on the diary (Figure 2), the weekly mean frequency of CSBMs from day 0 (week 0) to day 14 (week 2), day 28 (week 4), and day 42 (week 6) will be evaluated [32, 54, 55] (Table 1).

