### 2.14. Data Collection and Collation

The defecation diary (Figure 2) completed by the volunteers will be collected online daily, and the DASS-21 (Appendix 6) will be collected online as scheduled (see Table 1). One stool sample for the gut microbiome analysis and one for the metabolomics test will be collected from each volunteer on days 0 (preadministration period), 28 (administration period), and 42 (postadministration period); these samples will be stored separately and sent for tests at a temperature of −80°C in a special stool storage kit from Guangdong Longsee Company (https://www.longseemed.com).

An independent data management team (DMT) will be established to maintain and monitor study quality and safety. The data of individual characteristics, defecation diary entries (Figure 2), and DASS-21 data (Appendix 6) completed online by volunteers will be downloaded as Excel spreadsheets for further analysis. The gut microbiome and metabolomic data from stool samples will be examined by the Key Laboratory of Dairy Biotechnology and Engineering, Ministry of Education. All data will be submitted to the DMT for management and monitoring. The DMT will promptly analyse the data and contact collectors to resolve any uncertainty that occurs. All records that contain names or other personal information that could identify a participant, such as ID number or consent forms, will be stored separately from the study records. The database will be password protected by the DMT. The team will also have the authority to conduct an interim analysis or terminate the study's next step if the following situations occur: (1) if the probiotic does not affect the gut microbiome, then the study team will not conduct tests on the faecal metabolomes; and (2) if any severe adverse events related to the probiotics occur, the DMT will suggest terminating the study.

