In addition, the statistical analyses of metagenomic and metabolomic data will be performed using *R* software (v.4.0.2) and Adobe Illustrator. PCA and PLS-DA will be performed and visualized using the *R* packages vegan, ggplot, and ggpubr, and the adonis *P* value will be generated based on 999 permutations. The *t*-test, Wilcoxon test, and Kruskal–Wallis test will be used to evaluate differences in variables between and within groups; *P* values will be corrected for multiple testing using the Benjamini–Hochberg procedure. Meanwhile, Pearson's and Spearman's correlation coefficients will be calculated to analyse the correlations between different indicators in clinical, metagenomic, and metabolomic data.

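### Data analysts are declared blinded, but section 2.5 opens the randomization sequence at the interim and final analyses without limiting who sees it

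*Protocol article*

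**What the plan says.** The abstract (Method) makes the claim without a time limit: "Volunteers, treatment distributors, data collectors, and data analysts will be blinded".

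Section 2.5 makes it with one: "During the study, the volunteer's treatment distributors, data collectors, and data analysts will be blinded to the randomization sequence". The next sentence covers custody and release. "The randomization sequence will be maintained by an independent project administrator", and the sequence "will only be unblinded in the case of major safety issues or when performing the interim and final data analyses". It does not say who receives the opened sequence at either analysis.

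Section 2.14 assigns the interim to the data management team (DMT), which it describes as independent: "The team will also have the authority to conduct an interim analysis or terminate the study's next step". Two situations are listed: no effect of the probiotic on the gut microbiome, in which case the metabolome tests are dropped, and severe adverse events related to the probiotic. The same section has the DMT receive and monitor all data, control access to the database, analyse incoming data promptly and go back to the collectors about anything uncertain.

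**The concern.** Blinding an analyst protects the trial only while that person works on data: settling queries, deciding exclusions, assigning participants to the completer and compliance sets of section 2.15, deriving outcomes and producing outputs. A rule that opens the sequence when the analyses are performed releases it during exactly that work.

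At an interim more is at stake. If the code goes to the team that runs the interim, the people resolving queries on data still being collected may know the arms. Judgements on incomplete or odd diary entries could then, even without intent, differ between arms.

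There is also a reporting problem. The Discussion presents blinding as strictly followed, Table 2 marks it as met for this trial, and the design is offered as guidance to others. The trial would be credited with analyst blinding that its own release rule does not secure.

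**Working it through.** No figure in the plan bears on this point, and the sample size in section 2.12 is unaffected. The check is a comparison of the statements, stage by stage.

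| Stage | Abstract | Section 2.5, blinding | Section 2.5, release | Do they agree? |
|---|---|---|---|---|
| Conduct, no analysis under way | Analysts blinded | Analysts blinded | Major safety issues only | Yes |
| Interim analysis | Analysts blinded | Analysts blinded, since the interim falls within the study | Sequence opened | Only if analysts and data cleaners are kept from it, which is not stated |
| Final analysis | Analysts blinded | Depends on when the study is taken to end | Sequence opened | Section 2.5 can be read consistently; the abstract is not secured |

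**Interim.** There are two readings.
- (a) The opened sequence goes to the DMT. The team that handles queries then knows the arms before data are complete, against the blinding sentence in section 2.5.
- (b) It goes to a third party who reports only a result. Blinding then holds.

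The text does not choose between them.

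**Does the interim need true arm identity?** Whether the probiotic changes the microbiome is a comparison of two arms, and a test of a difference can be run on arms labelled A and B. The second situation concerns adverse events, for which section 2.5 already has a separate safety exception. On the wording of section 2.14, neither situation requires the people who clean or analyse the data to hold the whole sequence.

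**Final analysis.** If the study ends with follow-up, the blinding sentence in section 2.5 has expired when the code is opened, and the section is consistent with itself. The abstract has no such limit, so its claim holds only if the analysts work without the code. Nothing in section 2.5 requires that.

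**The case against.** The strongest reply is that section 2.5 limits analyst blinding to the period of the study, so opening the code for a final analysis after follow-up contradicts nothing and is common practice. The abstract merely condenses that sentence. The text never says analysts receive the sequence; it stays with an independent administrator. Coded labels, database lock and order of sign-off are usually left to a statistical analysis plan or full protocol, neither of which is shown.

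Much of this stands. Final-analysis unblinding is not in itself an error, the absence of those procedural details is not the finding, and that analysts will know the arms is an inference, not a statement of the plan.

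It does not dispose of the point. An interim analysis lies inside the period for which section 2.5 promises blinding, so the time limit cannot reconcile the two sentences there. Calling the DMT independent does not help, because independence is not blinding and the same team resolves data queries. An unseen analysis plan might name a separate unblinded party, but section 2.5 would still state a release rule without that limit, beside an abstract that claims blinding without qualification.

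**Conclusion.** The point holds as an unreconciled safeguard. The conflict is direct at the interim and weaker at the final analysis, where only the abstract's unqualified claim is left unsecured. It is worth correcting because the remedy is nearly free, but it does not undermine the design. It assumes that an interim, if held, takes place before follow-up ends, and that opening the sequence means more than unmasking a single participant.

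Three stronger readings are tempting, and the documents do not support them.

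- **That analyst blinding fails.** The recipient of the sequence is not named, so failure cannot be concluded.
- **That the harm can be sized as an inflated false-positive rate from choosing among diary windows for the weekly mean.** That inflation would come from a window not being fixed, not from knowing the arms. For a rank-sum test, U_A + U_B = n_A × n_B, so swapping labels leaves |U − n_A × n_B / 2|, and hence the two-sided p-value, unchanged. An analyst seeing only A and B could pick the smallest p-value just as easily. Coding the arms would not cure this; fixing the window would, and that is a separate matter.
- **That unblinded analysts have a free choice of test for the trial's main outcomes.** The list in section 2.15, "Wilcoxon test, and Kruskal–Wallis test will be used to evaluate differences in variables between and within groups", concerns the metagenomic and metabolomic data. For the frequency of complete spontaneous bowel movements, the same section names one between-group test.

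What coding does protect against is judgement that depends on direction: settling queries, exclusions or derivations in the knowledge of which arm is the probiotic. The documents give no basis for putting a number on that.

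**What to change.** Amend section 2.5 as follows.

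1. Interim and final analyses are run on arms coded A and B, with the code supplied by the independent administrator who already holds the sequence.
2. The code is revealed only after database lock and after sign-off of the outcome derivations and the primary and secondary outputs. Performing the analyses is removed as a reason to open the sequence; the existing safety exception stays as it is.
3. If an interim needs true arm identity, it is handled by someone who takes no part in data queries or the final analysis, and section 2.14 is aligned with this.
4. If the sponsor prefers to analyse with the code open, the abstract is restated so that it does not claim analyst blinding at analysis.

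Two practical cautions follow from using group codes. Unmasking one participant for safety reveals the code for the whole arm to anyone holding the coded data, so it should not reach the analysts. Species-level microbiome results may also suggest which arm received *L. plantarum*, so the derivations of the clinical outcomes should be signed off before those results are seen, or the two sets of analyses should be kept with different people.

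The cost is protocol wording and one coded group variable, with no extra participants or data. Section 3.1 reports 130 of the planned 200 enrolled, leaving 200 − 130 = 70 still to enter, so at that status the change can be in place before the final analysis.
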